### Randomisation and allocation

Participants will be assigned to the intervention or control group using stratified 1:1 randomisation with mixed block sizes to maximise the chances of equal allocation to groups. The participants will be stratified by hospital site and sex (male, female, intersex). Participants will not be blinded as to their group allocation. This is because of obvious differences between the intervention and standard care. The hospital staff who are delivering wound care will be aware of the patient’s allocation status. Emergency unblinding will not be required as the study will not be blinded. Randomisation will take place at enrolment.

Randomisation will be implemented in the electronic data capture system used by the clinical trials unit. The sequence generation will be based on a random seed, selected by the study statistician, who will have no prior knowledge of the allocation sequence until after generation.

Participants will be allocated a treatment arm in the electronic case report form, via a randomisation form, where allocation details will be stored online and an email notification sent to the study team. Access to the online randomisation system will be via personal username and password, and specific to role.

If participants are no longer eligible for randomisation, they will be considered ‘consented, but not randomised’ and will not contribute to the required sample size.

### Intervention

#### Standard care group

Participants will receive standard surgical wound care follow-up, but not the digital wound monitoring with AI module. Standard wound follow-up after cardiac surgery may include an outpatient visit or telemedicine appointment 4–6 weeks after surgery, advice to contact the general practitioner (GP) or the hospital if the patient has concerns, and a postdischarge SSI surveillance questionnaire through the post or over the phone at 30 days.

### Digital wound monitoring with AI module group

Participants in the intervention group will receive the digital wound monitoring with an AI module in addition to standard surgical wound care follow-up. Participants will not be aware of AI output. Only clinicians interact with the AI component.

Isla is a browser-based digital platform which is used to monitor patients’ surgical wounds by collecting self-reported data (wound images and questionnaire responses) in response to preprogrammed regular short message service (SMS) text or email messages. Patients can use Isla on any modern phone, tablet or computer, there is no App to instal or download. Staff access is through existing tablets used in hospitals. The data are reviewed by clinicians, and patients are informed that there are no wound healing concerns or are contacted to obtain additional information or prescribe treatment.

The component under investigation in this study is a new module for the Isla platform which uses AI to identify signs of non-healing on wound images. Non-healing signs are redness or discolouration, wound gaping, unexpected tissue or fluid, or removable stitches or surgical clips detected more than 14 days after surgery. While clinicians will review all images, the images identified by the AI platform will be put forward for urgent priority review by Isla software. The new wound prioritisation module is being validated for predictivity, sensitivity and specificity, and inter-rater reliability.

Patients will receive verbal and written information on how to respond to SMS text messages and email links. Patients in the intervention group will be contacted via SMS text message, or email if preferred, 7 days, 14 days and 21 days after surgery with the link request remaining open for 6 days until the next request is sent out. For each request, patients are asked to submit a photo of their wound and complete the UK Health Security Agency (UKHSA) wound surveillance questionnaire.^21^

### Outcome measures

#### Safety outcomes

The primary safety outcome is the quality of images received, assessed by clinicians at 30 days. A quality image is one that can be used to make a clinical decision.

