**Methods and analysis:**

This is a feasibility study for a new artificial intelligence module with 120 cardiac surgery patients at two centres serving a range of patient ethnicities and urban, rural and coastal locations. Each patient will be randomly allocated using a 1:1 ratio with mixed block sizes to receive the platform with the new detection and prioritising module (for up to 30 days after surgery) plus standard postoperative wound care or standard postoperative wound care only. Assessment is through surveys, interviews, phone calls and platform review at 30 days and through medical notes review and patient phone calls at 60 days. Outcomes will assess safety, acceptability, feasibility and health economic endpoints. The decision to proceed to a definitive trial will be based on prespecified progression criteria.

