#### Sample size

This is a feasibility study, and therefore, sample size calculations cannot be calculated as there are no current data which can be used as the basis of the calculations. The feasibility outcomes for this study are all binary outcomes, for which the widest CIs will occur with a proportion of 0.5 (or 50%), therefore, calculating a sample size for the CI based on 50% gives a ‘worst case’ estimate.

Recruiting 60 patients for each treatment group into the trial (ie, a total of 120 patients) will enable us to estimate the recruitment and drop-out rates with a 95% CI of within ±10% even if the rates were 50% for these two feasibility outcomes. (The 95% CI for a sample size of 120 patients and 60 successes, ie, 50% of patients recruited, or 50% of patients completing the study, is 41% to 59%). If the adherence to treatment rate is 50%, the adherence rate and 95% CI could be estimated to within ±13%. (The 95% CI for 30 adherent patients out of 60, as this is only relevant for patients in the intervention group, is 37%–63%). The sample size estimations were calculated using STATA V.18 with command ‘cii proportions’.

In addition, national data show a wound problem rate of 21% (our data shows 15%) with a cardiac wound infection rate of 8%.^19 20^ A sample size of 120 patients should provide around nine patients in each group with a wound problem of which 4–5 patients should have a wound infection. This is sufficient to inform feasibility, safety and acceptability data.

With a potential sample size of 1300 patients, we plan to recruit 120 patients over 10 months, a recruitment rate of around 11%. This should be achievable as a randomised trial using patients’ smartphones to monitor surgical wounds had a 69% recruitment rate.^9^

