#### Other secondary outcomes

Additional data collected are the number of photos received per patient, number of wound images/non-wound images, number of quality images, number of requests for images that are complied with, number photos initiated by patients, number of follow-up requests and number of wound images correctly prioritised.

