### Data collection

Data collected at 30 days after surgery will be through an online survey, online interviews for a subset of participants, questionnaire-based phone calls and a review of the Isla platform data. 30 days has been chosen as the data collection point as this is the recommended follow-up time for a wound infection as stipulated by the national wound surveillance programme run by the UKHSA.^20^ Further data are collected at 60 days to estimate quality of life and identify events such as hospital readmissions or further surgery which will be used in the health economic analysis. Data collected at 60 days after surgery will be through questionnaire-based phone calls and medical case note review.

Online surveys will be hosted on Dacima. The patient survey will focus on satisfaction with wound follow-up (and acceptability of the platform for intervention group participants only). Staff surveys will focus on satisfaction with wound monitoring including the Isla platform with AI. The survey is expected to take 10 min to complete. Interviews will be conducted via Teams, recorded using digital audio recording and transcribed. The focus of the patients’ interviews will be acceptability of the Isla platform, satisfaction with postoperative wound follow-up and acceptability of taking part in the study. Interviews are expected to last around 40 min. The Isla platform review will be conducted to collect data on the number of images submitted, dates of submissions and discrepancies between Isla wound prioritisation and clinician prioritisation. Phone calls at 30 days will include the UKHSA postdischarge SSI questionnaire to diagnose wound infection status, questions focusing on engagement with National Health Service (NHS) services (including treatment, antibiotics, readmissions, further surgery, GP or hospital visits) and a quality-of-life tool (SF-6Dv2). The phone call at 60 days will focus on engagement with NHS services and will include the SF-6Dv2 quality-of-life tool. Medical case note review will capture demographic data plus readmissions or further surgery.

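### The only named primary safety outcome is image quality, which cannot show a concerning wound that the AI module fails to prioritise, and no safety result enters the progression criteria

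*Protocol article*

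**What the plan says.** All references are to the protocol article.

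- **What is tested.** Under Digital wound monitoring with AI module group: "The component under investigation in this study is a new module for the Isla platform which uses AI to identify signs of non-healing on wound" […]. The same section says that clinicians look at every image, and that "the images identified by the AI platform will be put forward for urgent priority review by Isla software". It also reports that validation of the module, including its sensitivity and specificity, is under way. No result is given.
- **Safety outcome.** "The primary safety outcome is the quality of images received, assessed by clinicians at 30 days". The definition follows: "A quality image is one that can be used to make a clinical decision". No other outcome is named under Safety outcomes. Data analysis has safety outcomes summarised as frequencies and percentages, while feasibility outcomes get 95% confidence intervals.
- **Data on prioritisation.** Other secondary outcomes lists the "number of wound images correctly prioritised". Data collection says that the platform review records submission dates and "discrepancies between Isla wound prioritisation and clinician prioritisation". Neither is called a safety measure.
- **Decision.** The abstract says: "The decision to proceed to a definitive trial will be based on prespecified progression criteria". Table 1 has three rows: recruitment, adherence with the module, and loss to follow-up. The stated objectives list safety first.
- **Sample size.** After projecting about nine wound problems per group, 4–5 of them infections, the section concludes: "This is sufficient to inform feasibility, safety and acceptability data".

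**The concern.** The module sorts images into priority or standard review. The failure peculiar to it is a false negative: a concerning wound left in the standard queue. Whether a photograph is clinically usable is a different property. Every image could be usable while the module prioritised none of the concerning wounds, and the primary safety outcome would still read 100%.

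The nearest listed measure does not fill the gap. A count of correctly prioritised images credits the module for every healing wound it leaves alone. Since most wounds are expected to heal, that count can look good while the concerning ones are missed.

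At stake is the reading of the trial. A favourable safety summary and three 'Proceed' ratings in Table 1 could be reported together without anyone having had to look at missed flags before deciding on the definitive trial.

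**Working it through.** **1. The plan's own figures.** Exact (Clopper-Pearson) 95% intervals are 40.7% to 59.3% for 60/120 and 36.8% to 63.2% for 30/60. These match the stated 41%–59% and 37%–63%. Expected events per group of 60 also match:

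- Wound problems, own data: 60 × 0.15 = 9.0
- Infections: 60 × 0.08 = 4.8
- Wound problems, national rate: 60 × 0.21 = 12.6, about 13

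The stated intervals concern recruitment, drop-out and adherence. None concerns safety.

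**2. What the event counts say about missed flags.** Only the intervention group has module output, so n is the number of affected patients in that group. In the most favourable result, no misses, the upper limit of the exact two-sided 95% interval for the miss rate is 1 − 0.025^(1/n).

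| Patients | If all submit an image | If 80% submit an image |
|---|---|---|
| Wound problem, 15% | n = 9: 33.6% | 48 × 0.15 = 7.2, n = 7: 41.0% |
| Wound problem, 21% | n = 13: 24.7% | 48 × 0.21 = 10.1, n = 10: 30.8% |
| Infection, 8% | n = 5: 52.2% | 48 × 0.08 = 3.8, n = 4: 60.2% |

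The 80% column uses the 'Proceed' line for adherence in Table 1 (60 × 0.80 = 48).

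Seeing no misses is also weak evidence. If true per-patient sensitivity were 80% (an assumption; the document gives none), the chance of no miss among nine patients is 0.8^9 = 13%. At an assumed 90% it is 0.9^9 = 39%.

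**3. Why the pooled count can mislead.** As an illustration, assume one image per intervention patient, nine of them concerning, and a module that prioritises nothing. All nine concerning images are missed, yet (60 − 9)/60 = 85% of images are correctly prioritised. With 13 concerning images the figure is (60 − 13)/60 = 78%.

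**4. Route from safety data to the decision.** Data analysis ties the definitive study to Table 1. Its three rows use consent, image submission and completion. None uses image quality, prioritisation accuracy or wound outcomes.

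**The case against.** The case for leaving the plan alone has four parts.

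- **Clinicians review every image, and intervention patients also keep standard wound follow-up.** This stands and limits the severity. A reader might infer that infected wounds could go unseen, but the document supports only delay. Delay still matters, because the stated aim includes speeding up treatment.
- **The hazard is already measured.** Correct prioritisation and discrepancies are recorded, and wound problems, diagnosis dates, readmissions and further operations are secondary feasibility outcomes. This also stands. The defect is in how the data are designated, summarised and used, not in missing data.
- **Accuracy is being validated separately, and a feasibility trial need not estimate it.** This is reasonable, and the article says the study is not powered for effectiveness. But no validation result is shown or tied to Table 1, and the sample size section does claim adequacy for safety.
- **An outcome with so wide an interval tells little.** This is true of it as proof of accuracy. It rules out a fixed accuracy threshold or an automatic downgrade: with four imaged infections and an assumed 90% sensitivity, at least one miss would occur with probability 1 − 0.9^4 = 34%. It does not argue against reporting the count and its uncertainty.

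Two further readings are tempting but unsupported. One is that the trial could declare its safety outcome met; no threshold is set, so there is nothing to meet. The other is that the raters who judge correct prioritisation have already seen the module's ordering. The article implies that treating clinicians see it, but does not say who supplies the reference rating or under what conditions.

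**Conclusion.** The point holds in a limited form. The sole named primary safety outcome measures the input to the module and cannot register a missed flag. The data that can are placed among other secondary outcomes, in a form that pools true positives with true negatives. No safety result enters the table that decides progression.

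The claim that the expected events suffice for safety is not supported for this hazard. With no misses observed, the upper 95% limit on the miss rate would be about 25% to 34% for wound problems and 52% for infections, or 31% to 41% and 60% at 80% submission.

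These limits assume that the 15%, 21% and 8% rates apply to the intervention group, that patients with a wound problem stand in for patients with a clinician-concerning image, and that submitting an image is unrelated to having a problem. Because all images are reviewed, this is a modest, inexpensive correction and not a fundamental flaw. Adverse-event reporting may be in the full protocol and is not counted as missing.

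**What to change.** 1. **Outcome.** Alongside image quality, name as a safety outcome the number and proportion of intervention patients with at least one image that the clinician judged concerning and the module did not prioritise. The denominator is all intervention patients with a clinician-concerning image. Link each judgement to the date of that image and report an exact 95% confidence interval. The day-30 telephone diagnosis should not be the reference: the last scheduled request is on day 21 and stays open for 6 days, so an infection arising after the last photograph would be counted as a miss by the module.
2. **Table 1.** Add a safety line under which any missed flags are reviewed before a 'Proceed' decision, without a fixed accuracy threshold.
3. **Sample size.** Replace the statement that the numbers are sufficient for safety with the achievable precision: with zero misses, upper limits of about 34% (0/9) or 25% (0/13) for wound problems and 52% (0/5) for infections, wider if only 80% of patients submit an image.

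The cost is wording and one table line. Module prioritisation, clinician prioritisation and submission dates are already part of the platform review. Masked re-rating of images would add a procedure and is not needed for this change. The downside is that a wide, purely descriptive interval is stated openly.

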#### Acceptability outcomes

Primary acceptability outcomes are clinician and patient satisfaction using surveys and interviews at 30 days, acceptability of the intervention including attitude, burden, perceived effectiveness, ethicality, understanding, opportunity costs and self-efficacy. Acceptability data will also include the acceptability of being involved as a study participant. Secondary outcomes, and more detailed reasons for compliance/non-compliance with digital monitoring, will be explored in the patient intervention group surveys and interviews, and the staff surveys and interviews.

#### Feasibility outcomes

Primary feasibility outcomes are the recruitment rate, adherence with the module (defined as submission of one photo during the 30-day period), loss to follow-up and reasons for loss to follow-up. Secondary outcomes are access/barriers to participation and willingness of participants to be randomised, attrition rates, suitability of assessment procedures and outcome measures (including time and resources required to conduct assessments), number and severity of wound problems/infections, date of diagnosis, wound-related hospital readmission, further surgery to treat wounds, prescribed wound treatments, prescribed antibiotics, clinic visits and GP visits.

#### Health economic outcomes

Primary health economic outcomes include the number and severity of wound problems/infections, wound-related hospital readmissions, time to review images, further surgery to treat wounds, prescribed wound treatments, prescribed antibiotics, clinic visits, GP visits, patient travel time and quality-of-life data (SF-6Dv2).

#### Other secondary outcomes

Additional data collected are the number of photos received per patient, number of wound images/non-wound images, number of quality images, number of requests for images that are complied with, number photos initiated by patients, number of follow-up requests and number of wound images correctly prioritised.

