For all secondary outcomes, continuous variables will be reported using descriptive methods such as means and 95% CI. Categorical variables will be reported with frequencies and percentages.

There will be no subgroup analysis, no adjusted analysis and no interim analysis.

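### The only listed outcome on AI accuracy is an undivided count of correctly prioritised images, which cannot show how many concerning wounds the module missed

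*Protocol article*

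**What the plan says.** The aim of the trial (Protocol article, Introduction) is to assess a platform whose AI helps clinicians by putting concerning wound images forward for urgent review.

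In the outcome sections, accuracy of that sorting appears once. Other secondary outcomes ends its list of additional data with the "number of follow-up requests and number of wound images correctly prioritised". What counts as correct is not defined, and urgent and standard images are not separated. For secondary outcomes the Data analysis section states: "Categorical variables will be reported with frequencies and percentages". It promises 95% intervals for feasibility outcomes and for continuous secondary variables, but not for categorical ones.

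Three other statements bear on the point:

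- The section on the digital monitoring group says that the module is being validated for sensitivity, specificity, predictivity and inter-rater reliability, and that clinicians look at every image.
- Data collection says the platform review will record "discrepancies between Isla wound prioritisation and clinician prioritisation".
- Sample size says: "A sample size of 120 patients should provide around nine patients in each group with a wound problem".

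**The concern.** A triage tool can fail in two ways: it can leave a concerning wound in the standard queue, or it can send a sound wound to the urgent queue. The two errors have different consequences, and concerning wounds are expected to be the minority. One undivided figure cannot show both errors.

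- If it counts correct urgent plus correct standard images, the many images without a problem dominate it. A high percentage is then compatible with zero sensitivity.
- If it counts only images rightly put forward, missed wounds are absent from it.

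At stake is what the feasibility trial hands on. A high percentage could be taken into the definitive trial as evidence that prioritisation works when it says little about misses. A percentage without an interval also hides how few concerning wounds lie behind it.

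**Working it through.** **Inputs from the article (Sample size).** 60 patients in the intervention arm; per-patient wound-problem rate 21% nationally and 15% in the team's own data; infection rate 8%.

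**The plan's own figures.** 60 × 0.15 = 9.0 wound problems and 60 × 0.08 = 4.8 infections per arm. These match the stated nine and 4–5. The nine therefore rests on the 15% rate; 21% would give 12.6.

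**Overall agreement.** With p the share of images that need urgent review, Se the sensitivity and Sp the specificity:

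share correct = p × Se + (1 − p) × Sp

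A module that never flags has Se = 0 and Sp = 1, so it scores 1 − p.

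**Size of p.** The article gives no image-level value, so p has to be assumed:

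- p equal to the per-patient wound-problem rate: 1 − 0.21 = 79% and 1 − 0.15 = 85%.
- Affected patients show signs on one of three images: 1 − 0.21/3 = 93% and 1 − 0.15/3 = 95%. With the 8% infection rate, 1 − 0.08/3 = 97%.
- Affected patients send three images and others one: p = 3r/(3r + 1 − r). For r = 0.21, p = 0.444 and the score is 56%. For r = 0.15, p = 0.346 and the score is 65%.
- Broad signs on 30% to 50% of images: 70% to 50%.

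The never-flag score thus runs from about 50% to 97%. The top end uses infection, which is narrower than what the module looks for; on the wound-problem rates the top is 95%.

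**Order of two illustrative modules.** Module A has Se 50% and Sp 95%; module B has Se 95% and Sp 80%. A scores higher when

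0.50p + 0.95(1 − p) > 0.95p + 0.80(1 − p), that is 0.15(1 − p) > 0.45p, that is p < 0.25.

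- At p = 0.15: A = 0.075 + 0.8075 = 88%; B = 0.1425 + 0.68 = 82%.
- At p = 0.21: A = 0.105 + 0.7505 = 86%; B = 0.1995 + 0.632 = 83%.

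Above 25% the order turns round, but the figure still hides the direction of error. At p = 0.50, Se 60% with Sp 95% and Se 95% with Sp 60% both score 77.5%.

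**Flagged images only.** A never-flag module scores zero, so this reading exposes it. Images that should have been flagged and were not still do not enter the count.

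**Precision for misses.** With 0 misses in 9 affected patients, the exact two-sided 95% upper limit is 1 − 0.025^(1/9) = 34%. With 8 of 9 detected, the exact interval for sensitivity is 52% to 99.7%. Both take one image per affected patient and assume that all nine send one.

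**The case against.** The strongest reply is that the article does not commit itself to a pooled percentage. It lists a number among additional data, leaves its denominator open, and adds one general sentence on categorical variables; the cross-tabulation may be in the full protocol or analysis plan. It is true that the detail may be there. But the article names the outcome and how it will be summarised, and on either reading that summary is a poor one for a two-way sorting tool. The point concerns the choice made, not a missing detail.

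A reader might infer that AI accuracy is measured nowhere else. The documents do not support that: sensitivity and specificity are named in the description of the module, and discrepancies with clinicians are to be recorded. What stands is narrower. Neither is listed as an outcome of this trial, and a statement that validation is under way does not make it one.

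A reader might also take 79% to 92% as what a useless module would score. That treats per-patient rates as image-level prevalence, and the upper end uses infection. The module looks for a wider set of signs, such as redness, gaping, and stitches or clips still present after two weeks.

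Finally, one might infer that an unsafe module could pass into the definitive trial on this figure. Table 1 rests on recruitment, adherence and loss to follow-up only. One module is tested, so nothing is ranked. An unflagged image is still reviewed, though without priority, and a module that never flagged would show up in the discrepancy data.

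**Conclusion.** The point holds as a weakness of one descriptive secondary outcome. Under overall agreement, a module that flags nothing scores 79% to 85% if image-level prevalence equals the per-patient wound-problem rates, and about 50% to 97% across the assumptions shown. For any prevalence below 25%, a module with sensitivity 50% and specificity 95% outscores one with sensitivity 95% and specificity 80%. Counting flagged images only removes the first problem but leaves misses out.

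These figures rest on an assumed image-level prevalence and on illustrative sensitivities and specificities; the article gives none of them. No progression decision depends on the item. The consequence is a potentially misleading account of prioritisation performance carried into the definitive trial. It is a cheap improvement, not a flaw in the design.

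**What to change.** In Other secondary outcomes, replace the single count with the 2x2 table of module against clinician prioritisation, taken from the platform review already planned, with the clinician's prioritisation named as the reference. From it report:

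- sensitivity: of the images that clinicians judged to need urgent review, the proportion flagged, with the number missed;
- specificity: of the images judged not to need it, the proportion left in standard review;
- a 95% interval for each that allows for several images per patient, since three requests are scheduled;
- sensitivity per patient with an exact 95% interval, stating beforehand what counts as detection in a patient who sends more than one urgent image.

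State that the pooled percentage will not be used as evidence that prioritisation works.

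The cost is outcome and analysis wording; no new data are needed. The downside is a less flattering result with a wide interval for sensitivity: with about nine affected patients, even no misses leaves a miss rate of up to 34% possible. That uncertainty is there in any case, and the definitive trial should be planned with it in view.
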